### Data entry and quality control

We will collect the data using standardized forms and measurements. A trained research assistant will collect data at baseline (T0), before discharge from the nursing home (T1), 4 months (post-intervention) (T3) and at 6 months (follow-up) (T4). All data will be entered into a database (Castor, http://castoredc.com), according to Academic Medical Centre Good Clinical Practice Guidelines with an identification code for each patient.

The sensor monitoring data of the patient will be kept under the identification code and stored in a secured database.

According to the good clinical practice guidelines, data will be stored for 15 years and archived according to the regulations of the Netherlands Federation of University Medical Centers (NFU) (http://www.nfu.nl).

### Statistical analysis

An adapted CONSORT flow diagram will detail the flow of clusters and patients through the trial (see Fig. 1). Baseline comparability at the level of clusters (immediately after randomization) and patients (at recruitment) will be assessed. Descriptive data will be used to assess any time trends of patient characteristics at recruitment since patient selection bias is a threat in cluster trials that cannot be blinded for allocation.

The treatment effects (OTc vs control, OTcsm vs OTc, and OTcsm vs control) on the various outcomes will be estimated with mixed linear models using dummy variables for the two treatments, random intercepts for the clusters, and time as a fixed effect. For each outcome, the baseline values of that outcome will be used as a covariable [56]. The trial will have limited power to explore treatment by time or treatment by cluster interactions. If feasible, we will explore these. Two sided 95% confidence intervals will be calculated.

An intention-to-treat analysis will be the primary analysis. Per-protocol analyses based on degree of compliance with the study protocol will be used in an exploratory fashion.

A descriptive qualitative and quantitative analysis will be conducted on the data from the evaluation forms of the participants and the assessors and the data from the therapists of a given intervention. We will analyze the qualitative data based on the constant comparative method [57].

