## Background

Each year in the Netherlands, 17,000 people are admitted to a hospital after a hip fracture. The effects of a hip fracture are serious; one year after a hip fracture, 25% of patients have died and 20–90% of older individuals have new Activities of Daily Living (ADL) disabilities, defined as a functional decline [1–3]. Risk factors for functional decline after hip fracture can be divided into non-modifiable and modifiable risk factors. Non-modifiable risk factors are older age, female gender, living alone, cognitive impairment (dementia) and comorbidities. The modifiable risk factors are activities of daily living (ADL), walking ability, and depression [4–6]. Psychological factors such as low levels of self-efficacy and fear of falling have also been associated with functional decline after hip fracture in older individuals [7, 8].

Currently, most multidisciplinary rehabilitation programs for patients after hip fracture concentrate on improving mobility and ADL function but not fear of falling [7]. The evidence on the effectiveness of these rehabilitation programs on the recovery of ADL function is mixed. Exercise interventions have been used to improve physical function (e.g., gait speed, mobilization, balance, and strength), but despite an improvement in physical function, many older persons do not achieve a full recovery of ADL function [9, 10]. High-intensity (e.g., 4 times a week physical therapy) and intensive extended supervised exercise programs (e.g., during 12 month) had a significant impact on various physical functions, but the cost-effectiveness of these extended programs is unclear [11]. The main component of effective studies is ‘home-based functional task exercises’ (e.g., walking stairs, transferring), which results in a modest improvement in physical function post-discharge or at one year after discharge [12].

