### Randomization procedure

Randomization was performed, 4 weeks before the start of the study, by the second author, who was not involved in the day to day logistics of care delivery. A dedicated program was written using the sample command in Stata version 13.1 (Stata Corp LP, College Station, TX) applying the following principles: (i) centers were ranked as to their size and likely patient recruitment potential; (ii) three strata were formed, 2 largest, 2 intermediate-sized and the 2 smallest centers; (iii) these were allocated in a way that would enhance the likelihood of collecting similar amounts of information the 3 strata across the 6 time periods; (iv) in particular, we forced the intermediate-sized centers in the 2-2-2 months periods; (v) we randomized the remaining 4 centers such that 1 large and 1 small center followed the 1-2-3 months periods and the other pair the 3-2-1 months periods, respectively.

Figure 1 shows the flow of clusters and participants through the trial using an adapted CONSORT diagram [27].

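### The stated model adjusts for no patient characteristic beyond the baseline outcome, so a patient-mix shift that follows each home's crossover is left partly uncorrected

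*Protocol article*

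**What the plan says.** The Statistical analysis section specifies "mixed linear models using dummy variables for the two treatments, random intercepts for the clusters, and time as a fixed effect". It adds one patient-level term: "For each outcome, the baseline values of that outcome will be used as a covariable". No other patient covariate appears, either in the main model or in a sensitivity model.

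On selection, the section states: "Descriptive data will be used to assess any time trends of patient characteristics at recruitment since patient selection bias is a threat". Baseline comparability of clusters and patients is also to be assessed.

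Three other parts of the article bear on this.

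- **Timing.** Under Randomization procedure: "Randomization was performed, 4 weeks before the start of the study". Under Recruitment of patients, nursing home physicians identify candidates after admission. A research assistant then informs them, checks eligibility and obtains consent.
- **Prognosis.** The Background says: "Non-modifiable risk factors are older age, female gender, living alone, cognitive impairment (dementia) and comorbidities". It lists ADL, walking ability and depression as modifiable factors.
- **Data.** Table 3 and the section on medical and demographic variables show that age, gender, comorbidities, MMSE and Katz-15 are recorded at baseline.

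**The concern.** Patients are identified and give consent when the home's current condition is already known. Therapists are trained before each switch. OTcsm also asks the patient to wear a monitor and to accept a sensor network at home for three months. Willingness to approach a patient, or to consent, could therefore change when a home crosses over, for instance if fewer cognitively impaired patients enrolled under OTcsm. Eligibility starts at an MMSE of 15, which leaves room for such a shift.

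A shift of this kind moves with the treatment dummies. Tabulating it afterwards shows that it happened but does not correct the estimate. The article names the threat, names prognostic factors and collects them, yet does not put them in the model it writes out. At stake are some bias in the treatment contrasts and a modest amount of precision.

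**Working it through.** **1. What each stated term can remove**

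| Source of difference in patient mix | Term that handles it |
|---|---|
| Calendar trend common to all homes | Fixed time |
| Stable difference between homes | Random cluster intercept |
| Shift at each home's own crossover, reflected in the baseline outcome | Baseline outcome covariate |
| Shift at each home's own crossover, not reflected in the baseline outcome | None |

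Only the last row is at issue.

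**2. Reproducing the plan's figures**

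Inputs from Sample size calculation and Table 1: 6 clusters, 6 steps, 8 patients per cluster per step, ICC 0.05, effects of 1.5 SD (OTc versus control) and 0.75 SD (OTcsm versus OTc). Sequences from Randomization procedure are 1-2-3, 2-2-2 and 3-2-1, two homes each, read here as numbers of two-month steps. Two-sided alpha of 0.05 is taken from the planned 95% intervals.

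- Patients: 6 × 6 × 8 = 288, as stated.
- Generalised least squares with a random cluster intercept, categorical steps and two incremental treatment dummies, total SD = 1: SE = 0.2387 for effect 2.
- Power for effect 2: Φ(0.75/0.2387 − 1.96) = Φ(1.18) = 88.2%. Power for effect 1 is 100.0%.
- Reading SD as the within-cluster SD gives 86.5% for effect 2. A t reference gives 85.8% with 28 df and 84.8% with 20 df.

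The stated 85% and 100%, obtained by simulation, are consistent with this. Neither figure is in error.

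**3. Size of the bias (shift and coefficients assumed)**

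Let s be the shift in a standardised prognostic index among OTcsm recruits, b its coefficient on the 6-month outcome given the baseline outcome, and ρ its correlation with the baseline outcome. With the baseline outcome already in the model, the bias is b × s × (1 − ρ²). Take ρ = 0.3, so 1 − ρ² = 0.91.

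| s | b | Formula | Simulated, stated covariate only | Simulated, index added |
|---|---|---|---|---|
| 0 | 0.2 to 0.4 | 0 | −0.012 to −0.006 | −0.007 to −0.006 |
| 0.3 | 0.2 | 0.055 | 0.052 | −0.008 |
| 0.3 | 0.4 | 0.109 | 0.099 | −0.007 |
| 0.5 | 0.2 | 0.091 | 0.098 | 0.005 |
| 0.5 | 0.4 | 0.182 | 0.175 | −0.002 |

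The simulation used 600 runs per setting, a true effect 2 of 0.75 SD, and cluster dummies in place of random intercepts. Its Monte Carlo error is about 0.24/√600 = 0.01. The simulated bias runs from 0.052/0.75 = 7% to 0.175/0.75 = 23% of the planned effect, or from 0.052/0.239 = 0.2 to 0.175/0.239 = 0.7 standard errors.

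**4. Size of the precision gain (extra R² assumed)**

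The first power column shrinks the residual variance in the model of step 2. The second starts from the stated 85% and takes Φ(2.996/√(1 − R²) − 1.96), where 2.996 = 1.960 + 1.036.

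| Extra R² | SE, effect 2 | Power from 88.2% | Power from 85% |
|---|---|---|---|
| 5% | 0.233 | 89.5% | 86.7% |
| 10% | 0.228 | 90.9% | 88.5% |
| 20% | 0.216 | 93.5% | 91.8% |

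The gains are 1.4 to 5.4 points and 1.7 to 6.8 points. If the planning figure leaves out the baseline outcome and that covariate correlates 0.5 with the 6-month outcome, power starts at 94.7% and the same range of R² reaches 95.6 to 97.8%, a gain of 0.8 to 3.0 points.

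**The case against.** The strongest objection is that this is a journal article. A fuller covariate list may stand in an analysis plan that is not shown, and the article never says that the baseline outcome is the sole covariate. That limits the point but does not dispose of it. The article writes the model out term by term, raises the selection threat beside it, and gives a descriptive response. The criticism is of that stated model.

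It is also fair that the response is not purely descriptive. Adjusting for the baseline outcome is an analytic step, eligibility is explicit, and a research assistant checks it. For Katz-15, POMA and TUG, the baseline value itself measures ADL or mobility, which the Background names as risk factors. The gap is therefore narrower for those outcomes than for the COPM.

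Three stronger readings are tempting but unsupported.

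- A reader might infer that the restricted allocation makes matters worse, since "we forced the intermediate-sized centers in the 2-2-2 months periods" and only 2 × 2 = 4 allocations remained. But selection after allocation would be just as possible with many more allocations.
- A reader might infer that baseline COPM is a weak proxy for prognosis because patients choose the problems they rate. The article gives no figure on its prognostic value.
- A reader might multiply a shift by a marginal correlation and treat the product as the bias. Because the baseline outcome is in the model, the partial coefficient is the relevant one, as in step 3 of the working.

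**Conclusion.** The point holds in a limited form. As written, the model leaves in the treatment contrasts any crossover-linked change in patient mix that the baseline outcome does not capture. The prognostic factors that could partly correct this are named in the article and already collected.

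The bias is potential. Nothing in the document shows that recruitment will differ by condition, and with no shift there is no bias under either model. For assumed shifts of 0.3 to 0.5 SD and coefficients of 0.2 to 0.4, it is about 0.05 to 0.18 SD. Adjustment removes only the part carried by measured factors; motivation or willingness to accept sensors would remain. The gain in power for OTcsm versus OTc is roughly 1 to 7 points for an assumed extra R² of 5 to 20%. OTc versus control is already at 100%.

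A reader might infer that the sample size is wrong or the trial underpowered. The reproduced figures do not support that. This is a worthwhile, low-cost improvement to the analysis and does not threaten the design.

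**What to change.** Prespecify in the primary model, for every outcome, a short set of individual-level fixed covariates besides the baseline value of that outcome: age, sex, baseline MMSE and one comorbidity measure. The comorbidity measure needs a written definition, because the article says only that comorbidities are recorded. Baseline Katz-15 may be added, but not a second time when Katz-15 is the outcome. Living alone is an entry criterion and so cannot usefully serve as a covariate.

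Keep the currently stated model as a sensitivity analysis, and keep the descriptive time trends, which help in judging whether a shift occurred. Settle the set before outcome data are examined by condition.

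The cost is wording, four or five individual-level terms if each is entered as a single term (against 288 patients), and a stated rule for missing baseline covariates so that patients are not dropped. No new data collection is needed.

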## Discussion

The present three-arm stepped wedge randomized trial combines CBT principles that have been successful in the treatment of fear of falling and the multidisciplinary rehabilitation of older adults with hip fracture with the incorporation of sensor monitoring in the intervention as a coaching tool (monitoring and feedback tool) to improve daily functioning, physical activities, sense of safety and reduce the fear of falling at home. To our knowledge, this is a first trial evaluating the effectiveness of these interventions in older individuals after hip fracture.

Stepped wedge designs with more than two interventions have, as far as we know, never been used. Because we make use of restricted randomization we will reduce the between-cluster variation and improve balance, which is advisable when there are few clusters [58].

The use of a stepped wedge design provides us some methodological and practical advantages. First, the intervention effect can be estimated using between and within cluster comparisons and the professionals are their own controls in the interventions [59]. Second, each participating nursing home will have implemented both interventions at the end of the study while in a traditional cluster randomized trial some clusters will have received only a control intervention. This increased nursing homes’ willingness to participate. Third, in order to provide training in each cluster before the start of the interventions, the staggered start of the interventions makes a better time allowance. The same accounts for the technical support of the tool if needed. Last, because of the crossover from control to OTc and OTcsm and each participant receives only one condition, we may assume that there are no carryover effects [58].

For older adults, the ability to remain mobile is an essential aspect of quality of life and is crucial for the preservation of independence [15]. An important aspect of the intervention using sensor monitoring is to apply CBT principles. Sensor monitoring embedded in the OT intervention with CBT coaching is expected to have an impact directly at the level of the patient’s ability to perform activities in his or her own context. A characteristic of the use of sensor monitoring in an OT intervention is that goals related to daily activities are formulated that are relevant and important to the person and are based on the objective measurement of daily functioning by sensors. The coaching by the occupational therapist will target these particular issues. Our hypothesis is that the person’s self-perceived performance in daily activities, measured using the COPM, will alter as a result of the intervention.

This study will provide new knowledge regarding the combined intervention of CBT coaching by occupational therapists and CBT coaching by occupational therapists using sensor monitoring, enabling older individuals to perform everyday activities and to remain living independently after hip fracture.

## Abbreviations

ADL: Activities of daily living
CBT: Cognitive behavioral treatment
COPM: Canadian Occupational Performance Measure
EQ5D: Euroquol, instrument for assessing health related quality of life
FES-I: Falls Efficacy Scale-International
IADL: Instrumental Activities of Daily Living
Katz-15: Katz Index of Independence in Activities of Daily Living
MDS: Minimal dataset
MMSE: Mini Mental State Examination
OT: Occupational therapy
OTc: Occupational Therapy with Coaching
OTcsm: Occupational therapy with coaching and sensor monitoring
PAM: Physical Activity Monitor
POMA: Performance Oriented Mobility Assessment
PT: Physical therapy
SO-HIP: Sensor monitoring embedded in Occupational therapy rehabilitation for patients after Hip-fracture
SO-HIP tool: Sensor monitoring system used for hip rehabilitation
VAS-SAFE: Visual Analogue Scale for Fear of Falling
WMO: Medical research involving human subjects act
